**Synopsis**

This randomized, controlled study aims to figure out the role of probiotics in core symptoms and severity in children with autism. Secondary objectives are to determine whether probiotics regulate gastrointestinal disorders and sleep disturbances which often troubled children with autism, as well as its effect on blood and fecal metabolites, intestinal flora, and immune system.

Patients aged 3 to 12 years will be eligible if they are defined as having ASD by two child psychologists using DSM-5, but if they meet one of the following exclusion criteria they will not be allowed to take part: (1) they have taken antibiotics or antifungal drugs within three months; (2) they have a special diet, such as a gluten free diet, a casein diet, or a special carbohydrate diet; (3) they have taken prebiotics, probiotics, or antioxidants within the previous three months; (4) they have had diarrhoea, fever, or other clear inflammatory reactions within the past week; (5) they have neurological symptoms such as epilepsy; (6) they have Crohn’s disease, inflammatory bowel disease, food intolerance, or any other gastrointestinal diseases; (7) they have a liver disease; (8) they have type 1 diabetes mellitus; (9) they have a confirmed diagnosis of Rett syndrome or any other genetic metabolic disease.

All participants will be provided written informed consent before they approved to take the probiotics as required. The patients will be divided into treatment group and control group according to their severity, gender and age randomly. The treatment group will receive probiotics treatment for three months before three months withdrawal. The control group will be given the same amount of maltodextrin. The treatment and nursing of the two groups are in accordance with the same standards.

Therapeutic effect evaluation will be done at 1, 2, 3, 6 and 12 months after taking probiotics. 3, 6, 12, and 18 months by the ATEC, CSHQ, Birstol and other scales. The primary outcome was whether probiotics could alleviate poor language and cognition, narrow interest ranges, and gastrointestinal and sleep disorders in children with autism.

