**Hypotheses**

Primary: Probiotic supplements could relieve the core symptoms of autism，such as the narrow range of interests or activities and repetitive and stereotypical behavior.

Secondary(a): Probiotics can help balance gastrointestinal disorders in children with autism, such as constipation and diarrhea.

Secondary(b): Metabolites from the gut flora help improve sleep disorders.

Secondary(c): The metabolites of intestinal flora contribute to the improvement of immunity.

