**Assessment of** **core symptoms**

All parents/guardians will be asked to complete an Autism Treatment Evaluation Checklist (ATEC) ^[32]^ to evaluate changes in core symptoms in Children with ASD at the time of the baseline, the third month, and the sixth month respectively. The scale consists of four subscales: speech, perception, social interaction, and behaviour. The total score is 0-179; the higher the score, the more serious the condition. The reduction rate of ATEC score before (S1) and after (S2) treatment will be used as the efficacy index (N), N = (S1- S2)/S1 × 100%. Markedly effective: NM ≥ 50%, Effective: NE: 20%−50%, Ineffective: NI < 20%. Total effective rate (NT) = (NM + NE) / total cases × 100%.

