**Follow-up**

**1,2,3, 6,12months:** Assessment of Gastrointestinal tract, sleep, speech and communication skills, social skills, perceptual skills, health and physical behavior according to scale. (blinded assessment by certified study personnel)

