**Primary Outcome Measure**

- 1. Efficacy evaluation
  2. Severity of disease

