**Secondary outcome measures**

1. Gastrointestinal symptoms
2. Sleep
3. Parental pressure
4. Eating habits
5. Diet pattarns
6. Metabolites in Blood and fecal
7. Immune cells
8. Abundance of intestinal flora

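### The protocol contradicts itself on its primary outcome and on when the ATEC is measured, so the confirmatory test is not fixed

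*Protocol*

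**What the plan says.** **Primary outcome.** The last sentence of the Synopsis reads: "The primary outcome was whether probiotics could alleviate poor language and cognition, narrow interest ranges, and gastrointestinal and sleep disorders in children with autism". The opening of the same Synopsis reads: "Secondary objectives are to determine whether probiotics regulate gastrointestinal disorders and sleep disturbances which often troubled children with autism". The Hypotheses section limits the primary hypothesis to core symptoms and ranks the bowel and sleep effects below it, for example "Secondary(a): Probiotics can help balance gastrointestinal disorders in children with autism". Primary Outcome Measure lists two items, an efficacy evaluation and "Severity of disease", with no scale, visit or decision rule. Secondary outcome measures begins with "Gastrointestinal symptoms", and sleep follows. Study objectives puts core symptoms, gastrointestinal problems and sleep into one objective without ranking them.

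**Visits.** Assessment of core symptoms has the ATEC completed "at the time of the baseline, the third month, and the sixth month respectively". The Synopsis places efficacy evaluation at 1, 2, 3, 6 and 12 months, then adds "3, 6, 12, and 18 months by the ATEC, CSHQ, Birstol and other scales". Follow-up gives 1, 2, 3, 6 and 12 months.

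**Metric.** Assessment of core symptoms defines N, each child's percent reduction in ATEC from S1 (before treatment) to S2 (after treatment). It also defines NT, the proportion of children with at least a 20% reduction. It does not say which one is compared between groups.

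**Sample size.** The calculation uses a single two-sided alpha of 0.05 and 90% power, for outcome measures that it does not name.

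**The concern.** A confirmatory trial needs one identifiable test, or a stated rule for several. Here the sections give different sets of primary outcomes, different visits for the main scale, and two metrics from it. An analyst who followed the protocol faithfully could present any of several results as the primary one.

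The visit matters for interpretation as well as for error control. The Synopsis describes three months of treatment followed by three months' withdrawal. A month 3 comparison asks whether the product works while it is taken. A month 6 comparison asks whether any effect lasts after it is stopped. The trial could succeed on one and fail on the other, and the protocol does not say which question it was set up to answer.

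**Working it through.** **1. Which outcomes are primary?**
- Synopsis, last sentence: language and cognition, interests, gastrointestinal disorders, sleep. That is four domains if language and cognition count as one.
- Synopsis, opening: core symptoms and severity are the aim; gastrointestinal and sleep outcomes are secondary.
- Hypotheses: core symptoms only; gastrointestinal and sleep outcomes are secondary.
- Primary Outcome Measure: efficacy and severity. The ATEC section calls its reduction the efficacy index, and the CARS section is headed as severity, so the natural reading is ATEC and CARS.
- Secondary outcome measures: gastrointestinal symptoms and sleep are secondary.

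The last sentence of the Synopsis therefore conflicts with the other sections that rank the outcomes. With that sentence set aside, two primaries remain, and the Hypotheses section covers only one of them.

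**2. Which visit supplies S2?**
- ATEC section: 0, 3, 6 months.
- Synopsis (first list) and Follow-up: 1, 2, 3, 6, 12 months.
- Synopsis (second list, which names the ATEC): 3, 6, 12, 18 months.

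Months 3 and 6 are the only post-baseline visits on every list. One is the end of dosing and the other follows withdrawal. The CARS section gives no post-baseline visit.

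**3. False-positive rate if any single success is enough.** Each test is at two-sided 0.05. For k independent tests the rate is 1 − 0.95^k. For correlated tests it was simulated with equicorrelated normal statistics (400,000 draws).

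| Tests | corr. 0 | 0.3 | 0.5 | 0.7 |
|---|---|---|---|---|
| k = 2 (ATEC, CARS) | 1 − 0.9025 = 9.75% | 9.5% | 9.0% | 8.4% |
| k = 4 (two scales × two visits, or four Synopsis domains) | 1 − 0.8145 = 18.5% | 17.4% | 15.6% | 13.1% |

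**4. If both must succeed.** There is no inflation. Assuming 90% power for each test, joint power is 0.90 × 0.90 = 81% if they are independent, and between 81% and 90% if they are positively correlated.

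**5. Link to the sample size.** The stated 67 per group cannot be reproduced because no difference is given. Solving a two-group comparison for it, with SD 8.32, gives 8.32 × (1.960 + 1.282) × √(2/67) = 4.66 points. The SD belongs to a behaviour score that the protocol does not tie to ATEC or CARS. If alpha were split equally between two primaries (0.025 each), that difference would have 84.1% power at 67 per group. Restoring 90% would need 80 evaluable per group, or 80/0.81 ≈ 99 enrolled at the stated 19% drop-out.

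**The case against.** The strongest reply is that the conflict is narrow. The Synopsis aim, the two listed primaries, the ATEC and CARS sections and the secondary list fit together, and one Synopsis sentence is the outlier. The 3, 6, 12 and 18 month list is a sentence fragment and may be an editing remnant. With three months of dosing, month 3 is the natural reading of S2. This stands as a guide to what was probably meant. It does not supply a rule for two primaries, a visit for CARS, or a choice between N and NT, and the probable reading is not written down.

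A reader might infer that type I error is uncontrolled. The documents do not support that. The protocol states neither an any-success rule nor an all-must-succeed rule, and a multiplicity procedure may sit in a statistical analysis plan that is not shown. The absence of such a procedure is not the point here. The point is that any procedure needs a settled set of primaries, and the protocol gives conflicting ones.

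A reader might also infer that the ATEC rater changes between baseline and follow-up, because Follow-up speaks of "blinded assessment by certified study personnel" for domains resembling the ATEC subscales, while parents or guardians complete the ATEC elsewhere. Follow-up never names the ATEC, and the ATEC section assigns it to parents at every visit it lists. No change of rater is described, so this needs only clarification.

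Finally, five separately tested Synopsis domains would give 1 − 0.95^5 = 22.6%. That count splits language from cognition and assumes zero correlation, and the Synopsis does not say that each domain is tested on its own.

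**Conclusion.** The contradiction is real and should be resolved before any analysis. Gastrointestinal and sleep outcomes are both primary and secondary, two primaries are listed without a success rule, the visit lists for the ATEC conflict, and two ATEC metrics are left open.

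The size is conditional. Under any-success testing at 0.05, the familywise error would be about 8–10% for two primaries and about 13–19% for four tests, for correlations from 0.7 down to 0. The upper ends are unlikely, because two autism scales and repeat visits in the same child will be correlated. Under an all-must-succeed rule the cost would be power instead. That the confirmatory test cannot be identified from the protocol does not depend on either assumption.

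**What to change.** - Delete gastrointestinal and sleep disorders from the primary sentence of the Synopsis.
- State one primary in the same words in the Synopsis, Hypotheses, Assessment of core symptoms and Primary Outcome Measure. One example is the parent-completed ATEC at month 3, with the single tested metric named: change in total score, N or NT. Choosing change in total score would replace the efficacy index now in the ATEC section, so that section would have to be changed openly.
- For severity, either test CARS at the same visit second in a fixed sequence, or state that both outcomes must succeed. CARS then needs a stated post-baseline visit.
- Replace the conflicting visit lists with one schedule, and label visits after the primary one as persistence outcomes.
- Tie the sample size to the chosen endpoint, with its own SD and target difference.
- As a clarification, state in Follow-up which scales study personnel rate, and that the ATEC stays parent-completed at every visit.

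The cost is mostly protocol wording. Under the fixed sequence, error stays at 0.05 without splitting alpha, but severity can be claimed only if the ATEC test succeeds. Requiring both to succeed also holds the error rate but lowers power. Re-basing the sample size may change the number needed, because the present SD is not shown to apply to either scale.

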**Background**

**Ethical considerations**

Gut microbiota have attracted a good deal of attention in recent years. They maintain a stable symbiotic relationship with human beings in the intestines, which are regarded as a “second brain” because of the number of genes encoded by intestinal microbes (150 times the total genes of human cells) ^[1]^。Studies have shown that intestinal flora communicates with the brain through the nervous system ^[2]^、the immune system ^[3-6]^ and the endocrine system ^[7, 8]^，which leads to shifts in cognition, social behaviour, and emotion ^[9, 10]^。The abundance of the intestinal flora of Children with ASD undergoes great changes, whether between species or within species. Such as *Akkermansia*、*Coprococcus* and *Ruminococcus* are elevated and *Bifidobacterium* are decreased in Children with ASD^[11-14]^。The gastrointestinal symptoms and quality of life in ASD were improved by adding a mixture of *Lactobacillus* and *Bifidobacterium* to the diet ^[15, 16]^。

In this study, each volunteer’s guardian will sign an informed consent before taking probiotics, they be informed of the study process and precautions, and they can withdraw from the study for any reason during the process.

**Epidemiology**

Autism spectrum disorder (ASD) is one of the most prevalent neurodevelopmental conditions. It is marked by social and communication impairment as well as limited interests and stereotypical behaviours ^[17]^. The incidence of ASD has increased rapidly over time, from 0.31% in 2000 to 1.57% in 2009^[18, 19]^.It is estimated that 62.2 million individuals globally live with ASD ^[20]^. Moreover，the prevalence of ASD varies in different countries; for example, it is currently estimated to affect 1% of the general population in Spain^[21]^, 1.69% in the United States^[22]^ and 1% in China^[23]^. The core symptoms of ASD are narrow interests and rigid behaviours. A longitudinal study has suggested that people with ASD have poor outcomes, and that the lifetime cost of supporting an individual is a heavy burden^[24]^。.

**Probiotics**

The definition of probiotics was defined by the International Association for Probiotics and Probiotics Science is "a substrate that is selectively utilized by host microorganisms conferred health benefits" ^[25]^. Common probiotics: (1) Lactobacillus (such as Lactobacillus acidophilus, *Lactobacillus casei*, Lactobacillus Jennings, Lactobacillus Ramanei, etc.); (2) Bifidobacterium (such as *bifidobacterium longum*, *bifidobacterium brevis*, *bifidobacterium ovale*, *bifidobacterium thermophilus*, etc.); (3) Gram-positive cocci (such as *Streptococcus faecalis*, *Lactococcus*, *Streptococcus* intermediae, etc.); (4) Some yeasts and enzymes can also be classified as probiotics.

**Effects**

Probiotics has three main uses: (1) Treatment of ASD;(2) Balance gastrointestinal tract;(3) Regulating disturbed sleep

In recent years, studies on probiotics in children with ASD have shown that probiotics have great potential benefits in improving gastrointestinal dysfunction, malnutrition and ASD symptom severity ^[16, 26-28]^. In addition, its metabolic products also have a vital influence on the development of the nervous system.

For example, 5-hydroxytryptamine (5-HT) levels in the blood are associated with lower gastrointestinal symptoms in ASD^[29]^. Furthermore, the main neurotransmitters and hormones of gamma-aminobutyric acid (GABA) and melatonin are involved in sleep promotion, while serotonin, glutamate, and acetylcholine are mainly responsible for wakefulness^[30]^.

**Adverse effects**

Probiotics can cause uncomfortable gastrointestinal symptoms such as abdominal pain and diarrhea depending on the individual^[31]^.

**Study objectives**

The objectives of this randomized, controlled study are 1) to determine whether the probiotics treatment could relieve the core symptoms, gastrointestinal tract and sleep disorders of ASD. 2) to find out possible early biological markers of ASD. and 3) to figure out the possible pathogenesis of ASD.

**Hypotheses**

Primary: Probiotic supplements could relieve the core symptoms of autism，such as the narrow range of interests or activities and repetitive and stereotypical behavior.

Secondary(a): Probiotics can help balance gastrointestinal disorders in children with autism, such as constipation and diarrhea.

Secondary(b): Metabolites from the gut flora help improve sleep disorders.

Secondary(c): The metabolites of intestinal flora contribute to the improvement of immunity.

**Study design**

Experimental group: Oral probiotic mixture of 5 billion CFU/5g, twice a day in the morning and once in the evening respectively, for 3 months.

Control group: The same amount of maltodextrin, treatment course and usage were the same as experimental group.

Both groups were given the same nursing and diagnosis and treatment plan.

**PATIENT SELECTION**

**Inclusion Criteria**

1. Patients aged 3 to 12 years, gender unlimited;
2. Who diagnosed as ASD by DSM-5[17] definitely;
3. 3. Participate in the study and sign the informed consent voluntarily;

**Exclusion Criteria**

1. they have taken antibiotics or antifungal drugs within three months;
2. they have a special diet, such as a gluten free diet, a casein diet, or a special carbohydrate diet;
3. they have taken prebiotics, probiotics, or antioxidants within the previous three months;
4. they have had diarrhoea, fever, or other clear inflammatory reactions within the past week;
5. they have neurological symptoms such as epilepsy;
6. they have Crohn’s disease, inflammatory bowel disease, food intolerance, or any other gastrointestinal diseases;
7. they have a liver disease;
8. they have type 1 diabetes mellitus;
9. they have a confirmed diagnosis of Rett syndrome or any other genetic metabolic disease.

E**xit criteria**:

1. children who do not take the probiotics as required;
2. children whose blood and stool samples provide no biological information;
3. participants cannot complete DSM-5, CARS, and the other compulsory scales for ASD evaluation.

The children with autism who met the inclusion criteria and the exclusion criteria were randomly grouped according to gender, age and severity.

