**STUDY PROCEDURES**

Before the trial, all the children will be evaluated carefully, and the research topic will be explained to the parents of the Children with ASD who meet the study’s selection criteria. If they are then willing to participate in the trial, they will receive the supplements free of charge for three months and carry out the relevant inspections and tests. They will sign an informed consent agreement. They will be able to consult with the doctors if they have any questions when they are administering the supplements, but they must follow the requirements of the agreement. If they are not willing to continue the study for some reason, they can withdraw. All the potential side effects will be monitored and all the participants will be recalled at 3 months after intervention for the systematic physical examination and liver as well as kidney function analysis. The potential costs will be covered by indemnity for negligent harm. The participants will be asked to provide a one tube faeces sample 0, 1, 2, and 3 months after taking the supplements, and a tube of blood with heparin anticoagulation at 0 and 3 months. To guarantee quality all samples must be transported within 12 hours at low temperatures or they will be rejected. Other than the samples used for flow cytometry detection, which has to be completed within 12 hours, all samples will be aliquots and frozen in a freezer at -80℃.

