**Sample and data collection**

Peripheral Blood: A vacuum vasculture containing heparin anticoagulant was used to collect 1-2mL of peripheral venous blood at the time of baseline, three months after probiotics administration, and the deadline.

Stool samples: Fecal samples were collected at the baseline, three months after probiotics administration, and the deadline, respectively. Temporary storage in -20℃ refrigerator within 1 hour, transported in ice bags within 24 hours, -80℃ storage .

The information of candidate's gender, age, history of asphyxia, family history, history of allergies, diet and the mother's history of pregnancy, hypertension during pregnancy, mode of delivery need to collect. At the same time, the diagnostic results of DSM-5 and the evaluation results of ATEC, CARS, CSHQ, GSRS and so on also need to be recorded. These information can be used for subgroup analysis.

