**Sample size calculation**

The sample size will be calculated using Epitools (<https://epitools.ausvet.com.au/onemean>). The expected difference between the probiotic and placebo groups is based on a previous study on ASD, in which the standard deviation value of behaviour score was 8.32 in the ASD group^[31]^. To detect a clinically significant difference in the outcome measures with the condition of 90% power (α = 0.05; two-sided), 67 children are required for each group. Based on clinical study experience ^[40]^, we presume a drop-out rate of 19% through infection, efficacy, compliance, use of antibiotics, or other unforeseeable factors, implying a minimum of 80 children for each group.

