**Final Analysis**

The final analysis will be based on intent-to-treat and carried out after follow-up is closed for all patients in the study.

The analysis will include

- Source data listing
- An elementary descriptive analysis of all variables that were observed
- Assessment of the data quality that was achieved
- Description of study patients
- Assessment of drop-outs and the comparability of groups
- Evaluation of efficacy, including scheduled subgroups analysis
- Explorative analysis if further interesting results are suspected
- Biometrical assessment of the validity of the study results

In case there is an unexpectedly high proportion of dropouts, the most important parts of the analysis will still be done for all admitted patients (full sample analysis) as well as for those patients that can be used to test the efficacy of the treatment.

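### The protocol promises intent-to-treat, but its exit criteria let randomised children leave the study, for non-adherence among other reasons, and nothing keeps them in outcome follow-up or analysis

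*Protocol*

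**What the plan says.** Under Final Analysis the protocol states: "The final analysis will be based on intent-to-treat and carried out after follow-up is closed for all patients in the study". The closing paragraph of that section adds that, if drop-out is unexpectedly high, "the most important parts of the analysis will still be done for all admitted patients (full sample analysis"), alongside a second group of patients described only as usable for testing efficacy. Neither a threshold for high drop-out nor a definition of that second group is given.

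The exit criteria, listed at the end of Exclusion Criteria, are three: "children who do not take the probiotics as required"; "children whose blood and stool samples provide no biological information"; and participants who cannot complete DSM-5, CARS and the other compulsory scales.

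Sample size calculation requires 67 children per group and presumes 19% drop-out, "through infection, efficacy, compliance, use of antibiotics, or other unforeseeable factors", giving a minimum of 80 per group.

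The only explicit rule for continued follow-up is under Interim Analysis, and it covers early stopping of the whole trial. Study Procedures recalls all participants at 3 months, but for a physical examination and liver and kidney tests, not for the outcome scales.

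**The concern.** Intent-to-treat means that every randomised child is analysed in the allocated arm, whatever happens to adherence. An exit rule triggered by adherence works the other way unless the protocol says that exit stops short of follow-up and analysis, and this protocol does not say so. If sites apply the list as written, ATEC and CARS assessments may simply stop for children who exit, and no later analysis plan can recover outcomes that were never collected.

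Adherence can depend on the arm. The Adverse effects section says that probiotics can cause abdominal pain and diarrhoea, and efficacy is named as an expected reason for loss. If the children lost in one arm are mainly those doing badly and in the other arm they are not, the remaining children are no longer comparable and the comparison is biased.

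The sample criterion is a weak ground for leaving the trial at all. Uninformative blood and stool samples say nothing about the scales behind the primary outcomes of efficacy and disease severity.

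**Working it through.** **Step 1. The sections side by side.**

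| Section | What it implies for a randomised child |
|---|---|
| Final Analysis, first sentence | Analysed as randomised, without qualification |
| Exit criterion 1, not taking the product as required | Leaves; can occur only after allocation |
| Exit criterion 2, uninformative samples | Leaves; possible at month 0 or later, since samples are taken at baseline and afterwards |
| Exit criterion 3, incomplete scales | Leaves; possible at baseline (DSM-5 is a diagnostic item) or at follow-up |
| Sample size calculation | Compliance and efficacy losses are counted as drop-out |
| Final Analysis, last paragraph | All-patient analysis mentioned for the main parts when drop-out is unexpectedly high |

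Exit can hardly mean only stopping the product, because criteria 2 and 3 concern missing information and not the product. No section states the alternative, that an exited child stays in outcome follow-up and analysis.

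**Step 2. The plan's own figure.** 67 × 1.19 = 79.7, which rounds up to the stated 80. (Dividing, 67/0.81 = 82.7, gives 83; that is a separate matter.) With 80 enrolled and 19% lost, 80 × 0.81 = 64.8, so about 65 per group remain.

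**Step 3. How large the bias could be.** Assumed, not in the protocol: no true effect; 40% total effective rate in each arm if everyone is analysed; rate r among removed children of 20% or 10%. From the protocol: 80 per group, two-sided α = 0.05, 19% drop-out. If a share q of an arm is removed,

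kept rate = (0.40 − q × r)/(1 − q).

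For q = 0.19:
- r = 0.20: (0.40 − 0.038)/0.81 = 44.7%, a shift of +4.7 points.
- r = 0.10: (0.40 − 0.019)/0.81 = 47.0%, a shift of +7.0 points.

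For the 19%/0% split the arms have 64.8 and 80 children. With r = 0.20, the standard error of the difference is √(0.447 × 0.553/64.8 + 0.40 × 0.60/80) = 0.083, so the expected z is 0.047/0.083 = 0.57. The chance that |z| exceeds 1.96 is then 8.8%. The other splits follow in the same way, by normal approximation for the two-proportion test:

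| Removed, arm A / arm B | Type I error, r = 0.20 | r = 0.10 |
|---|---|---|
| 19% / 19%, equally selective | 5.0% | 5.0% |
| 21% / 17% | 5.2% | 5.5% |
| 24% / 14% | 6.4% | 8.2% |
| 19% / 0% | 8.8% | 13.6% |

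Simulation of the 19%/0% case gives 9.1% and 13.9%, in agreement. Equal counts alone do not protect: if both arms lose 19% but only one loses selectively, simulation gives 8.3% and 12.4%. Under equally selective removal the test keeps its size, but both arms' effective rates are inflated (44.7% or 47.0% against 40%).

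**The case against.** The strongest reply is that intent-to-treat is stated without qualification and governs. The exit list never says that data are dropped, and a child can leave treatment or the study and still be analysed as randomised. The word 'still' in the last paragraph of Final Analysis may be meant as reassurance that the full-sample analysis survives heavy drop-out, with an efficacy subset added. Inflating a sample size for expected loss is routine and compatible with intent-to-treat. Analysis-set definitions often sit in an SAP, which is not shown here.

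Much of this stands as a limit on the point. A reader might infer that the protocol expressly deletes exited children's data, or that the analysis set is to be chosen after seeing the drop-out rate. The text supports neither: it does not mention data deletion, and with high drop-out it calls for both analyses. Nor are all three criteria necessarily post-randomisation.

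The 9-14% figure is not what the plan implies. The 19% is presumed for each group and from all causes, and Randomisation and masking describes matched placebo with participants and doctors blinded, so a 19%/0% split is an extreme.

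A reader might also link the transport limits to exit: Study Procedures says "all samples must be transported within 12 hours at low temperatures or they will be rejected", while Sample and data collection has stool "transported in ice bags within 24 hours". That is a separate inconsistency. The 12-hour rule rejects a sample, not a child, and the exit criterion speaks of blood and stool samples together, so one late tube need not trigger exit.

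What the reply does not remove is that no section keeps an exited child in outcome follow-up or analysis. An SAP can define sets, but it cannot restore uncollected outcomes.

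**Conclusion.** The point holds as a conflict within the protocol. Intent-to-treat is promised, one exit criterion necessarily operates after randomisation and two may, compliance and efficacy losses are treated as drop-out, and exited children are nowhere retained. The last paragraph of Final Analysis adds doubt because it can be read as making the full-sample analysis conditional and partial, next to an undefined efficacy subset.

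The size cannot be fixed from the document. Under the assumed rates, type I error is near 5% if removal is equally selective in both arms, about 6-8% with a 24%/14% split, and about 9-14% in the extreme one-arm case. The reason to correct it does not depend on the upper figure: the conflict decides who is in the primary comparison, and the loss of outcomes would be irreversible.

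**What to change.** Reconcile the exit criteria, Sample size calculation and Final Analysis so that they say the following:

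- Meeting an exit criterion after randomisation does not end scheduled ATEC/CARS follow-up, unless consent is withdrawn, and does not end analysis in the allocated arm.
- Sample failure excludes a child only from the affected laboratory analysis.
- Incomplete follow-up scales are handled as missing data.
- The analysis of all randomised children is primary whatever the drop-out level. A defined adherent subset is a sensitivity analysis and replaces the undefined efficacy group.

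What non-adherence means for the study product itself is for the sponsor to reconcile. Separately, reconcile the 12-hour limit for all samples with the 24-hour limit for stool.

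The cost is a short amendment of a few sentences and some extra follow-up of children who would otherwise have exited, at visits that are already scheduled.
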